### **7.2.5 Composite allergy outcome**

1. The prevalence of combined allergic disease (a composite of cumulative IgE mediated food allergy to all foods, atopic wheeze phenotype, eczema and allergic rhinitis) at three years of age.
2. The prevalence of combined allergic disease (a composite of cumulative IgE and non-IgE mediated food allergy to all foods, atopic wheeze phenotype, eczema and allergic rhinitis) at three years of age.

## **7.3 Safety outcomes**

### **7.3.1.1 Adverse events – gastrointestinal symptoms**

*For each of these, the number of events will be analysed together with any associated morbidities or treatment as appropriate*

1. Diarrhoea
2. Constipation
3. Possetting
4. Vomiting
5. Colic

### **7.3.1.2 Adverse events – atopic symptoms**

1. Eczema
2. Wheeze – number of episodes, associated shortness of breath, A&E attendances, admissions

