#### **3. TRIAL ARMS**

**3.1 Early introduction group:** Dietetic controlled introduction of allergenic foods from three months of age. A pureed fruit / vegetable or baby rice mixed with breast milk or water commenced first, followed by cow's milk based yoghurt. Subsequently egg, sesame, fish, and peanut introduced in a randomized order, with wheat introduced last. (For further details on ingestion timing and quantities for each food, see protocol).

**3.2 Standard introduction group:** Standard introduction following current UK Government infant feeding advice (exclusive breastfeeding until around 26 weeks of age) and avoid introducing foods that may cause allergies before six months of age (cow's milk, egg, wheat, peanuts, tree nuts, seeds, fish and shell fish).

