#### **4.0 SAMPLE SIZE AND POWER**

The trial has 80% power to detect a 50% relative reduction in the absolute prevalence (from 8% in the standard introduction arm to 4% in the intervention arm) of food allergy by three years of age, assuming a 15%

drop out rate. These numbers were used to calculate the final cohort size of 1302 infants (651 infants in each arm) yielding a final cohort size of 1106 infants (553 infants in each arm) after drop out (based on the amended protocol September 2010). The whole cohort is to be followed up until the primary assessment point at three years of age.

The study is also designed so that it has sufficient power to detect a protective effect in the high risk sub-population. The high risk children are defined as being the 25% with eczema present at three months of age, who have an estimated prevalence of food allergy of 30%. It is estimated that with 15% loss to follow up, there will be 276 high risk children completing the study, 138 in each group. The study has 99% power to detect a reduction from 30% to 10% amongst the high risk participants in the intervention group and 85% to detect a reduction from 30% to 15%. See protocol (Protocol section 9.3: Contract variation September 2010). The study is not powered to detect a reduction in allergy to individual foods.

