## **7. ENDPOINTS**

### **7.1 Primary Endpoint**

The period prevalence of IgE mediated food allergy to the six intervention foods between one and three years of age in both arms.

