#### **7.2.2 Cumulative (by three years of age) prevalence food outcomes**

1. The cumulative prevalence of IgE mediated food allergy to the six intervention foods by three years of age.
2. The cumulative prevalence of all IgE mediated food allergy by three years of age.
3. The cumulative prevalence of all food allergy (IgE and non-IgE mediated) by three years of age.
4. The cumulative prevalence of non-IgE mediated food allergy by three years of age.
5. The cumulative prevalence of sensitization (defined in Section 3.9) to the six foods by three years of age.
6. The total number of foods (of the six intervention foods) to which IgE mediated food allergy has been diagnosed by three years of age amongst children with IgE mediated allergy to one or more of the six intervention foods.
7. The total number of foods (any foods) to which IgE mediated food allergy has been diagnosed by three years of age amongst children with IgE mediated allergy to one or more foods.

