#### **7.3.2 Serious adverse events**

1. Hospital admissions
2. All serious adverse events

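### No safety outcome separately counts allergic reactions to foods in the first year, and Table 5 has no row for such reactions or for all serious adverse events

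*SAP*

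**What the plan says.** Section 3 of the SAP describes the early arm as "Dietetic controlled introduction of allergenic foods from three months of age". The standard arm is told to "avoid introducing foods that may cause allergies before six months of age".

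The primary endpoint (7.1) is "The period prevalence of IgE mediated food allergy to the six intervention foods between one and three years of age in both arms". The period secondaries in 7.2.1 use the same window. First-year allergy enters through outcomes such as "The cumulative prevalence of IgE mediated food allergy to the six intervention foods by three years of age" (7.2.2), the composites in 7.2.5, and a one-year point prevalence in 7.2.3 that leaves out sesame and peanut.

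Section 7.3 itemises the safety outcomes:

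- **Gastrointestinal (7.3.1.1):** five symptoms, for which "the number of events will be analysed together with any associated morbidities or treatment as appropriate".
- **Atopic (7.3.1.2):** two entries, eczema and "Wheeze – number of episodes, associated shortness of breath, A&E attendances, admissions".
- **Infective (7.3.1.3):** four entries.
- **Serious (7.3.2):** hospital admissions and "All serious adverse events", with no limit on cause or age.
- **Other (7.3.3 to 7.3.7):** growth, behaviour, maternal, dietary and breastfeeding outcomes.

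Section 8.1.3 reports adverse events by arm as children, events and yearly incidence rates with 95% confidence intervals. Table 5 in 8.3.2 is the safety table for the main paper and has 11 items.

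**The concern.** The hazard most specific to this intervention is an immediate reaction to a food given early. Between three and six months the standard arm is meant to avoid these foods, so reactions to them in that period should fall mainly in the early arm. The safety list names many general infant symptoms but not this one.

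The primary endpoint opens at one year. A child who reacts at four months, is never admitted and tolerates the food by the first birthday is not a primary event and need not appear as a harm. The trial is meant to inform infant feeding practice (section 2), and that needs both sides of the account: allergy prevented later, and reactions met while the foods were being introduced. As written, the main paper would report the first clearly and could not isolate the second.

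**Working it through.** The point rests mainly on the outcome lists, so the first step is to trace where a first-year reaction would be counted.

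| First-year event | Counted in 7.3? | Row in Table 5? | Identified as a food reaction? |
|---|---|---|---|
| Serious reaction, not admitted | Yes, under all serious adverse events | No | No |
| Reaction leading to admission | Yes, under hospital admissions | Yes | No |
| Reaction with wheeze | Yes, if recorded as wheeze | Yes | No |
| Reaction with vomiting | Yes, if recorded as vomiting | No | No |
| Non-serious skin reaction such as urticaria or angioedema, not recorded as eczema | No | No | No |

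Table 5 lists diarrhoea, LRTI, constipation, eczema, wheeze, URTI, bronchiolitis, other infections, hospital admissions, and weight in two forms. Against 7.3 it omits, among others, vomiting and all serious adverse events, two items that could take in some reactions.

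Next, the efficacy outcomes a diagnosed child can enter:

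- **Allergy persists past one year:** primary endpoint and period secondaries.
- **Allergy resolved by one year:** the cumulative outcomes (Table 3 items 6 to 8, and 11 to 12 for the number of foods) and both composites (Table 4 items 7 and 8).
- **One-year point prevalence (7.2.3):** misses the resolved child, excludes two of the six foods, and is in none of Tables 3 to 5.

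These outcomes count children with a diagnosis, or foods per child. None counts reactions, repeat events or emergency attendances.

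Last, does a reaction row affect the design? Inputs from section 4.0: 8% v 4%, 80% power, 15% dropout; from 8.1.3: two-sided 5%.

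- n per arm = [z(0.975)·√(2·p̄·(1−p̄)) + z(0.80)·√(p₁(1−p₁) + p₂(1−p₂))]² / (p₁−p₂)²
- With p̄ = 0.06: [1.960·√0.1128 + 0.842·√0.1120]² / 0.04² = 553 after rounding up.
- 553 / 0.85 = 651 per arm; 2 × 651 = 1302.

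This reproduces the plan's figures (power at 553 per arm is 80.1%), and an added safety row leaves them unchanged.

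The SAP gives no reaction rate, so what such a row could show is illustrated with assumed rates at 651 per arm:

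- 1% v 3%: power about 73%.
- 1% v 2%: power about 32%.
- No events in 651 infants: one-sided 95% upper bound 1 − 0.05^(1/651) = 0.46%.

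Rates with intervals by arm would be informative even without a powered test.

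**The case against.** The strongest reply is that harm is already compared between arms. Section 7.3.2 limits neither cause nor age, so the gravest reactions are counted. Wheeze, vomiting and eczema catch parts of others, with associated treatment or attendance for some. Section 8.1.3 describes Table 5 as material for the main paper, so absence from it does not mean an outcome goes unanalysed. All of this stands. A reader might infer that first-year reactions are in no safety outcome at all; the document does not support that.

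A second reply is that first-year diagnoses are compared by arm. Comparing the all-IgE rows in Table 3 (items 1 and 7), or the primary row in Table 2 with Table 3 item 6, would show allergy that resolved before one year. This also stands in part. The subtraction works only if both rows use the same children, and it yields resolved diagnoses, not reactions. It says nothing about first-year reactions in children whose allergy persisted, or about reactions never diagnosed as allergy.

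A third is that the protocol, not shown, may define how reactions are captured. It may, so the point is confined to the outcome and table lists that the SAP itself fixes.

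Finally, a by-arm count would partly reflect when foods were eaten, under unblinded reporting (section 6). That is a reason for a footnote rather than for leaving the count out.

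**Conclusion.** The point holds in a limited form. No item in 7.3 separately counts allergic reactions to foods in the first year. Serious and admitted ones are captured without being identified as food reactions, and Table 5 shows only admissions. Non-serious ones are counted only if they happen to be recorded as another listed symptom. This is a reporting gap worth closing, not a contradiction or an error in the efficacy analysis.

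Its size in children cannot be stated. A reader might be tempted to take 651 × 8% = 52 expected allergic children per arm, assume that some share react before one year, and set the result against the planned primary difference of 553 × (8% − 4%) = 22. The document does not support that. It gives no such share; 8% is the standard-arm rate, whereas the 4% planned for the early arm gives 651 × 4% = 26; and children with persistent allergy are already primary events. The power figures above are illustrations under assumed rates.

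**What to change.** - Add to 7.3.1.2 and Table 5 a safety row, *IgE-mediated allergic reaction to a food, enrolment to 12 months*, by arm, in the format of 8.1.3: number of children, number of events, and rate with 95% confidence interval.
- Give a sub-row for the six intervention foods and, where recorded, the children who attended A&E or were admitted.
- Carry the all serious adverse events item from 7.3.2 into Table 5.
- Footnote that reporting is unblinded and that earlier exposure reveals existing allergy sooner in the early arm, so a difference between arms is not wholly extra allergy.

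The cost is SAP wording and a few table rows, with no change to sample size or to the primary analysis. First-year diagnoses are already needed for 7.2.2. The dates and number of reactions and the attendances they led to are not needed there, and the SAP does not show that they were collected. That should be checked first; if they were not, the row should be limited to what was recorded and say so.

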### **7.3.1.3 Adverse events – infective symptoms**

1. URTI
2. LRTI
3. Bronchiolitis

4. Other infections

#### **7.3.2 Serious adverse events**

1. Hospital admissions
2. All serious adverse events

#### **7.3.3 Anthropometric outcomes**

1. Weight, absolute and SDS at 3, 12 months and three years
2. Length, absolute and SDS, at 3, 12 months and three years
3. BMI, absolute and SDS, at 3, 12 months and three years
4. Head circumference, absolute and SDS, at 3, 12 months and three years
5. Mid upper arm circumference at 3, 12 months and three years
6. Skin fold thickness, subscapular and triceps, at 3, 12 months and three years

#### **7.3.4 Behavioural outcomes**

1. Sleep outcomes (duration, time to settle, number of wakings)
2. Food aversions outcomes

#### **7.3.5 Maternal outcomes**

1. Maternal quality of life at 3, 12 months and three years

#### **7.3.6 Dietary outcomes**

1. Macro nutrient status at 6, 12 months and three years

#### **7.3.7 Breastfeeding outcomes**

1. Percentage of mothers breastfeeding at 6 months
2. Percentage of SIG mothers exclusively breastfeeding to around six months
3. Total duration of breastfeeding

### **7. STATISTICAL ANALYSIS**

#### **8.1.1 Intention to Treat Analysis**

These will be the main analyses and the ones that are used to quantify the efficacy of the intervention. Only ITT results will be reported in the abstracts of the main publication and trial report.

All children allocated to each of the two study arms will be analysed together as representing that treatment arm, whether or not they received or completed the prescribed regimen. This will be done after the three year assessment for the period prevalence of IgE mediated food allergy to the six intervention foods between one and three years of age in both arms.

#### **8.1.2 Per Protocol Analysis**

These will be reported in the body of the paper after the ITT primary and ITT secondary analyses. They will be included for explanatory purposes only, and will not be reported in the abstract nor regarded as primary or secondary measures of the efficacy of the intervention.

##### Assessing the 'dose' of potentially allergenic food received

The following algorithm defines a scoring system that quantifies dose in a relatively simple way and yet allows the detection of a dose-response, albeit outside of the original randomization. Hence for each participant regardless of group, their score will be defined as follows:

- Each week up to 6 months of age (26 weeks) that a participant ate a particular food at 75% or more would be scored 1 and lesser consumption would be a zero
- Each food would therefore yield a total score of between 0 and a maximum of 13 (as max weeks=13)
- The scores will be summed over all foods to give a total food consumption score which will be categorized into quintiles
- The relationship between score quintiles and the primary outcome will be explored using logistic regression with a test for trend across the quintiles

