#### **8.1.3 Statistical Methodology**

Binary outcomes will be presented as proportions and relative risks with 95% confidence intervals, p values being calculated from the chi-square test or Fisher's exact test if numbers are small, with appropriate methods used for the calculation of CIs when numbers are small.

Continuous outcomes will be analysed using methods based on the Normal distribution where possible either if data are Normal or can be suitably transformed. Results will be presented as differences in means with 95% confidence intervals and modelled using multiple regression with baseline values as covariates.

Adverse events will be reported by treatment group, aggregated and given as number of children, total number of events, and incidence rates per year with 95% confidence intervals

Prognostic baseline variables will be inspected for any imbalance between the groups that is judged to be clinically important. If any such imbalance is observed, these variables will be included as covariates in sensitivity analyses for all key outcomes (please see section 8.2 below).

All analyses will be 2-sided with 5% significance level.

The sections below will outline the analyses for the main paper of the trial and describe what material will be reported in each table.

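### Pooled quintiles of the consumption score collapse because about half the cohort scores zero by design, and the trend across them mostly repeats the randomised comparison instead of showing a dose-response

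*SAP*

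**What the plan says.** SAP section 8.1.2, under the subheading on assessing dose, gives one point for each week up to 26 weeks of age in which a food was eaten at 75% or more of the intended amount. A food can score at most 13. Both arms are scored: "Hence for each participant regardless of group, their score will be defined as follows". The totals are then grouped: "The scores will be summed over all foods to give a total food consumption score which will be categorized into quintiles". A logistic regression tests for trend across the quintiles with the primary outcome. The stated purpose is to allow a dose-response to be detected.

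SAP section 3.2 has the standard arm "avoid introducing foods that may cause allergies before six months of age". That is the same window in which the score accrues.

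The SAP gives no rule for ties at zero, no version within one arm, no covariates for this model, and no handling of infants who stop a food after a reaction. It does say that the analysis lies outside the randomisation, is explanatory, stays out of the abstract, and is not an efficacy measure.

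**The concern.** A quintile rule needs a score that spreads over the whole cohort. Here one arm is meant to sit at a single value, zero, so the rule cannot give five groups of 20%. Someone would have to choose the categories after seeing the data.

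Pooling also undermines the purpose. If the lowest category is in effect the standard arm, any difference between arms appears as a trend across categories, whether or not more food meant less allergy among infants who were fed it.

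Finally, an infant who reacts to a food and stops it loses score, and is also more likely to be an outcome case. That produces a protective gradient without any benefit from dose. The result is to appear in the body of the main paper, where readers could take it as support for a causal dose effect.

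**Working it through.** **Inputs.** From SAP section 4.0: power of 80% for a fall in prevalence "from 8% in the standard introduction arm to 4% in the intervention arm", and 553 per arm (1106) left after 15% dropout. From section 8.1.3: "All analyses will be 2-sided with 5% significance level". From section 8.1.2: weekly 0/1 scoring and a maximum of 26 − 13 = 13 per food, so 6 × 13 = 78 over six foods.

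**The plan's own figures.** The usual two-proportion formula for 8% versus 4%, with no continuity correction, gives 553 per arm and power 0.801. 1106 / 0.85 = 1301.2, rounded up to 1302. These reproduce.

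**Quintile cut-points.** Let z_S and z_E be the shares scoring zero in the standard and early arms. With equal arms the pooled share is z = (z_S + z_E) / 2. Every percentile up to z equals 0.

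- Design case, z_S = 1 and z_E = 0: z = 0.50, so the 20th and 40th percentiles are both 0. Sizes are 553; 0; 0.60 × 1106 − 553 = 111; then 221 and 221. One simulated draw gave 553, 0, 112, 224, 217.
- With z_S = 1 and z_E = 0.20: z = 0.60, three cut-points fall on 0, and three groups remain.
- The second group stays empty while z ≥ 0.40. That means z_S ≥ 0.80 if z_E = 0, z_S ≥ 0.70 if z_E = 0.10, and z_S ≥ 0.60 if z_E = 0.20.

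**What the pooled trend measures.** In the design case the non-empty groups keep codes x = 1, 3, 4, 5 with shares 0.5, 0.1, 0.2, 0.2.

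- Mean of x = 0.5 + 0.3 + 0.8 + 1.0 = 2.6. Variance = 0.5 + 0.9 + 3.2 + 5.0 − 2.6² = 2.84.
- Early-arm mean = (0.3 + 0.8 + 1.0) / 0.5 = 4.2; standard-arm mean = 1. Between-arm variance = 0.25 × 3.2² = 2.56. So 2.56 / 2.84 = 90% of the variation in the category code is simply the arm.
- Now take 8% versus 4% with no dose relation within the early arm. Covariance of x with outcome = 0.5 × 0.08 + 2.1 × 0.04 − 2.6 × 0.06 = −0.032.
- Expected trend statistic = √1106 × (−0.032) / √(0.06 × 0.94 × 2.84) = −1.064 / 0.400 = −2.66. The chance of passing −1.96 is Φ(0.70), about 76%.

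Simulation with an assumed beta(2,2) adherence distribution agrees (76% to 77%). The same trend restricted to the early arm is significantly protective in about 2.5% of trials, the nominal rate.

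**Infants who react and stop.** The SAP gives neither the share who stop nor the number of foods stopped, so both are assumed and varied. Null simulation: 8% in both arms, 553 per arm, standard arm at zero, beta(2,2) adherence. The table shows the share of trials with a false protective pooled trend (nominal 2.5%), by share of early-arm cases who stop.

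| Foods stopped | 25% | 50% | 75% | 100% |
|---|---|---|---|---|
| One of six (about 5/6 of score kept) | 3% | 5% | 6% | 8% |
| Three of six | 6% | 17% | 34% | 58% |
| All six | 57% | 99% | 100% | 100% |

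The last cell uses the score test. The fitted logistic model breaks down there because no infant with a non-zero score is a case.

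The early-arm-only trend is more exposed. In a 4,000-trial check under the same assumptions, its false-protective rates were 8%, 20%, 39% and 62% with one food stopped.

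**The case against.** The strongest reply is that the SAP has already disclaimed this analysis. It is exploratory, acknowledged as non-randomised and kept out of the abstract, and efficacy rests on intention to treat alone. That stands, and it limits the severity. It does not supply a workable grouping rule or warn that a flat arm effect will look like a dose-response.

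Several stronger readings are tempting but not supported.

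- *The analysis cannot be run.* It can: a trend test still runs on four unequal ordered groups. Five unequal groups could also form if fewer than 40% of the pooled cohort scored zero. The fault lies in the categorisation and its interpretation.
- *The trend will be falsely protective because of reactors.* The direction is right, but the size is unknown. An infant who stops one food can still score up to 65 of 78. Nor is an early reactor automatically a case, since the primary endpoint covers one to three years of age.
- *Introduction order distorts the score.* Foods are "introduced in a randomized order, with wheat introduced last", so later foods cannot reach 13 weeks. But the score is summed before ranking. Under a common timetable, permuting the randomised foods leaves the maximum total unchanged, and a shared lower ceiling does not alter ranks.

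**Conclusion.** The point holds and should be fixed. If the standard arm largely follows its allocation, the stated quintiles do not exist and the lowest category is essentially that arm. A significant pooled trend then cannot be told apart from a plain difference between arms: about 76% of trials would show one under the planned effect with no dose relation. That figure assumes a standard arm entirely at zero and an early arm entirely above zero.

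Bias from early reactors runs towards protection and has no safeguard in the SAP. Its size is conditional on the assumptions above, from close to nominal when one food is stopped to near certainty when all are.

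A reader might infer that the trial's efficacy conclusion is compromised. It is not: the primary and secondary intention-to-treat analyses and the sample size are untouched.

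**What to change.** Reword the dose subsection of SAP section 8.1.2:

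1. Make a zero score its own category, shown by arm, and set cut-points in advance among early-arm infants with non-zero scores.
2. Report the dose trend within the early arm separately from the randomised contrast, and do not describe a pooled trend as a dose-response.
3. Add a sensitivity analysis that counts consumption only up to the first suspected reaction, divided by the weeks available to that point, and adjusts for eczema at enrolment (already in the section 8.2 baseline list).

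Items 2 and 3 belong together, because the within-arm trend is more open to reactor bias than the pooled one.

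A complier-average causal effect, with randomised arm as instrument, could be added. It answers a different question from dose-response. Its assumption that allocation acts only through consumption must be stated; with an adherence threshold, this includes no effect of intake below the threshold. It is optional.

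The cost is a paragraph of SAP text and a modest amount of extra analysis. Items 1 and 2 use consumption data the SAP already relies on; item 3 also needs the dates of suspected reactions, which the sponsor should confirm are recorded.

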#### **8.2 Description of baseline data: TABLE 1**

Key variables collected at baseline will be summarised by treatment group. For continuous variables; means and standard deviations will be calculated and for categorical data, actual numbers and the calculated proportions will be shown. No formal testing of baseline characteristics between treatment groups will be performed in keeping with best practice.

1. Sex of infant
2. Birthweight
3. Gestational age
4. Number of siblings
5. Age of mother
6. Maternal education
7. Maternal and paternal asthma/allergy
8. Maternal/paternal smoking
9. Ethnic origin of mother and father
10. Pet ownership status
11. Mode of delivery
12. Allergenic food consumption during pregnancy
13. Allergenic food consumption during lactation pre enrolment
14. Infant eczema status at enrolment

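### The dose-response model names no adjustment for enrolment eczema, so its trend can be confounded in a direction the SAP does not settle; minor, with no effect on the ITT result

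*SAP*

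**What the plan says.** Section 8.1.2 scores each infant's intake of the allergenic foods up to 26 weeks. Each food scores 0 to 13, the foods are summed, and the total is cut into quintiles. The analysis is then: "The relationship between score quintiles and the primary outcome will be explored using logistic regression with a test for trend across the quintiles". No covariate is named. The scoring covers both arms: "Hence for each participant regardless of group, their score will be defined as follows". The SAP says openly that the method "allows the detection of a dose-response, albeit outside of the original randomization". The opening of 8.1.2 limits these analyses to explanation, keeps them out of the abstract, and does not count them as efficacy measures.

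Three other places bear on the point:
- Section 8.1.3 has the only adjustment rule that could reach a binary outcome: "Prognostic baseline variables will be inspected for any imbalance between the groups that is judged to be clinically important". It leads only to sensitivity analyses, and it refers to section 8.2, where baseline data are summarised by treatment group.
- Section 4.0 says: "The high risk children are defined as being the 25% with eczema present at three months of age". It gives them a 30% prevalence of food allergy.
- Section 8.2 lists "Infant eczema status at enrolment" among the Table 1 variables, so the covariate is already collected.

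**The concern.** Once infants are grouped by what they ate, randomization no longer balances their baseline risk. Intake in the early arm depends on the family and the infant. A baseline factor that predicts both intake and allergy will produce or mask a dose trend.

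Enrolment eczema is the obvious candidate, because the SAP itself uses it to define the high-risk children. It can be evenly split between the arms, leaving the section 8.1.3 rule untriggered, and still be unevenly spread across dose quintiles.

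What is at stake is how the dose-response paragraph in the body of the paper is read. A trend that eczema alone could create or hide does not do the explanatory job it is given. This is confounding by a baseline variable. It is a different matter from covariate adjustment of the randomized comparison, where precision is the issue, and from infants who stop a food after reacting to it.

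**Working it through.** **The plan's own figures.** The SAP gives no figure for the dose model, so the check starts from section 4.0.
- For 8% v 4%, two-sided 5%, 80% power: n = [1.96·√(2·0.06·0.94) + 0.8416·√(0.08·0.92 + 0.04·0.96)]² / 0.04² = (0.6583 + 0.2817)² / 0.0016 ≈ 552.2, so 553 per arm, as stated.
- Dropout: 553/0.85 = 650.6, so 651 per arm and 1302 in total, as stated.
- High-risk children: 0.25 × 1106 = 276.5, against 276 stated. Power with 138 per arm is 98.8% for 30% to 10% and 85.1% for 30% to 15%, against 99% and 85% stated.

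**Implied risk without eczema (an inference).**
- (0.08 − 0.25 × 0.30)/0.75 = 0.005/0.75 = 0.67%, a risk ratio of 0.30/0.0067 ≈ 45.
- The figure is fragile. An overall prevalence of 7.5% makes it 0, and 7% makes it negative (−0.005/0.75).
- I therefore also use 3%, which implies an overall prevalence of 0.25 × 0.30 + 0.75 × 0.03 = 9.75%.

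**How the bias arises (early arm only, assumed shares, no food effect).** Let 35% of eczema infants and 55% of the others fall in the upper half of intake.
- Upper half: 0.25 × 0.35 + 0.75 × 0.55 = 0.50, of which eczema is 0.0875/0.50 = 17.5%. In the lower half eczema is 0.1625/0.50 = 32.5%.
- Risk, upper half: 0.175 × 0.30 + 0.825 × 0.0067 = 5.8%. Lower half: 0.325 × 0.30 + 0.675 × 0.0067 = 10.2%. Ratio 0.57.
- Reverse the gap (65% v 45%) and the two risks change places: 10.2/5.8 = 1.76, an apparent harm.

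**The planned pooled analysis, simulated with no food effect.** There are 553 infants per arm, 25% with eczema. The standard arm scores zero, because its families are told to "avoid introducing foods that may cause allergies before six months of age". Half the cohort is then tied at zero, and the early arm fills groups of 10%, 20% and 20% of the cohort. Early-arm intake is lower in eczema infants by an assumed number of SD. The table shows how often the two-sided 5% trend test rejects.

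| Intake deficit with eczema | Pooled, other infants 0.67% | Pooled, other infants 3% | Early arm only, 0.67% (not planned) |
|---|---|---|---|
| 0.25 SD | about 5% | – | about 19% |
| 0.5 SD | about 8% | about 6% | about 55% |
| 0.75 SD | about 13% | about 10% | – |

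Adding enrolment eczema to the model returns rejection to about 4–5%.

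**A second intake model.** Six foods over 13 weeks, with mean adherence of 50% without eczema and 45, 40, 30 or 20% with it. Pooled, a significant protective trend appears in 3, 6, 21 and 62% of trials, against a nominal 2.5%. With a 3% risk in other infants the figures are 3, 8, 16 and 48%. After adjustment they are about 1–4%. The pooled bias is thus small for gaps of 5 to 10 points and large only for gaps of 20 to 30 points.

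**The case against.** The case for leaving the text alone has four parts.

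**The SAP discloses and confines the analysis.** It calls the comparison exploratory and outside the randomization, and keeps it away from efficacy claims. This stands and limits the severity. It does not make an unadjusted trend informative.

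**The text is silent on covariates and does not rule them out.** That is true. But the model is otherwise spelled out, and the one adjustment rule looks at the wrong groups. An analyst following the SAP would fit the score alone or choose covariates after seeing the data.

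**Much of the pooled dose is set by allocation.** This also stands. The standard arm sits near zero in both eczema strata, which dilutes the bias. A reader might take the ratio of 0.57 or the 55% rejection rate as the size of the problem. Both come from an early-arm-only comparison, which the SAP does not plan.

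**Nothing in the SAP says that infants with eczema eat less.** This stands too. A reader might infer that the plan will manufacture a protective trend. The documents support only that the trend may be confounded. If families of infants with eczema kept to the foods better, the same omission would hide a benefit or suggest harm.

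**Conclusion.** The point holds as a minor one. The planned pooled trend names no adjustment for the strongest predictor that the SAP quantifies, and no other rule in the SAP supplies it.

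For intake deficits of 0.25 to 0.75 SD and no food effect, the false rejection rate rises from 5% to at most about 13% (about 10% if other infants carry a 3% risk). It becomes large only under wide adherence gaps. These sizes rest on three assumptions: the intake gap, its direction, and the non-eczema risk. The SAP states none of them, and the last is a residual of rounded planning figures.

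It would be wrong to conclude that the trial's efficacy finding is at risk. The ITT comparison does not use the dose score.

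**What to change.** Add one sentence to the dose subsection of 8.1.2: the logistic model for the trend across score quintiles will include infant eczema status at enrolment as a covariate, whatever the balance between arms. The eczema-adjusted trend will be the main dose-response result, with the unadjusted trend beside it. Other Table 1 variables, such as parental asthma/allergy, are optional. Any that are used should be named in advance and kept few, because events are few: 8% of 553 is about 44 in the standard arm and 4% is about 22 in the early arm.

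The variable is already collected, so the cost is the wording and the loss of any child with missing eczema status. Residual confounding remains, including from infants who stop a food after reacting to it, so the result should keep its explanatory label.
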